###### 2. Qualitative Data Collection

The purpose of qualitative data collection within the trial is to describe the experiences of participants and caregivers in the two arms relating to the care received (including acceptability and perceived effect), the impact of the illness and experiences of stigma and discrimination. We also intend to describe changes in these domains over the follow-up period, explore attributions of changes and to compare outcomes between the two arms of the trial.

We intend to recruit approximately 36 participants and 36 primary caregivers (= 36 participant - caregiver dyads) at each site for the in-depth-interviews at baseline; however, numbers may be increased if indicated by ongoing analyses. Separate consent will be obtained from participants and caregiver(s) for these qualitative interviews. The same participants and caregivers who are interviewed at baseline will be approached for follow-up interviews 12 months later after the final quantitative outcome assessments are completed.

The sampling strategy is purposive, taking into account participant's gender and the degree to which stigma is a concern to the participant as assessed by quantitative measures. Efforts will be made to purposively interview outliers. Sampling will further aim to ensure sample variability at each research site with regards to severity of illness, highest education levels in the household, type of relationship of caregiver to patient and other themes that may emerge as important from ongoing analyses.

In addition, we propose to conduct in-depth-interviews with Psychiatrists and CHWs at endpoint to ascertain their satisfaction with work, the adequacy of training and supervision and their impressions on the impact of the program.

####### Quality assurance and fidelity management

To ensure that the CCBC intervention is of adequate fidelity, we will collate the intervention process indicators related to the delivery of the intervention (Table 2) every month from each site. This will be monitored to check for significant divergence from per protocol norms between the sites; any such divergence will lead to suitable corrective action to harmonize the intervention across the sites.

For quality assurance purposes, key CCBC sessions at each site (needs assessment, 3 and 6 month reviews and termination session) will be rated by intervention coordinators during joint home visits with the CHWs. Feedback for improving the methods and delivery of the intervention will be provided to all CHWs to achieve and maintain pre determined quality benchmarks during the trial.

Systematic efforts will be made to ensure that both quantitative outcome measurements as well as qualitative interviews will be of adequate quality across the sites. The researchers will be supervised in a weekly group meeting with the study coordinators at each site. In addition, 5% of all interviews at each site will be assessed through joint onsite visits with the coordinator who will provide feedback using a specially designed assessment form to confirm that the overall pre-set quality benchmarks are achieved and maintained during the trial. For the qualitative data, there will be regular supervision available for researchers at each site with regular group and individual supervision related to interview methods, data translation and transcription.

To ensure the safety of the researchers while conducting interviews at the homes of participants, all initial visits will be made by a team of 2 researchers who will have notified the Coordinators about their location. Researchers have also been trained to recognize possible dangers and threats and respond to them appropriately (seating arrangements, non confrontational interview techniques). All researchers will also have access to mobile phones to discuss any potentially difficult situation with their supervisor. In case of any untoward incident, researchers will have provision for debriefing and a review of the safety arrangements.

##### Statistical issues

###### Sample size estimation

Based on the data from the earlier non randomized study[9], it was assumed that a difference of at least 20% reduction on the PANSS total score of 65 (sd 10) i.e. 13 points to 52, would be highly clinically significant. The estimated pre-post correlation was 0.4 (reducing the effective sd to 9 after adjusting for baseline). The intra-class correlation within the three sites in the control arm was set at 0.05; in the intervention arm (which would include within-CHW as well as within-site effects) it was set at a higher level of 0.1; alpha was set as 0.05. Using the method of Roberts and Roberts[28] with the Stata routine *cluspower *will give us 98% power to detect this difference. This is equivalent to a large standardised effect size, 1.44. For effect sizes of 1 (9 PANSS units) and 0.8 (7.2 PANSS units) the power would be approximately 90% and 80% respectively.

The required sample size of 241 was increased to 282 to allow for 15% attrition and rounded up to allow for a 2:1 randomisation within each site. The total number of participants was then divided slightly unequally between sites for reasons of feasibility. A total of 188 persons with schizophrenia will be allocated to the CCBC arm while 94 persons will be allocated to the FBC arm.

##### Data management and analysis

Findings will be reported according to the revised CONSORT guidelines[14]. No interim analyses are planned apart from baseline comparisons. The statistical package Stata will be used for the quantitative analysis. In accordance with good trial practices, data will be retained for 7 years after completion of the trial.

Descriptive summaries of socio-demographic and clinical data will be provided for all trial participants at baseline, and for outcome measures at baseline, 6-month and 12-month follow up points; this will include means and standard deviations, or proportions, in the two arms, as appropriate. Scale and subscale totals with missing items will be pro-rated (i.e. based on the mean of those items that are present) if 20% or fewer items are missing. The PANSS and the IDEAS will be summarised in terms of the total score, the separate sub scores of the different domains and the proportion of patients improving by >20% from baseline. Histograms within each arm will be used to assess normality of the distribution of the data, to identify any outliers and check for data errors. The proportion of participants who are fully, partially or non- adherent to antipsychotic treatment (derived from the adherence ratings of primary caregivers) will be reported for both arms. CHW characteristics such as completed years of education and caseload will also be described.

The data will be analysed under intention-to-treat assumptions (i.e. all those with at least one follow up measurement will be analysed in arms as randomised). The 12-month PANSS total score, adjusted for PANSS scores at baseline and site (using analysis of covariance), and including clustering effects of CHWs, will be used for determining the comparative effects of the two arms on this primary outcome of the study. The disability score generated by the IDEAS will be similarly analysed; in addition, a longitudinal analysis including both 6- and 12-month outcomes will also be performed using a GEE or random effects model including a time x treatment term allowing for modelling changes over time. Residual analysis will be performed to check the distribution of the data and to detect outliers. Logistic regression analysis with >20% reduction in PANSS at 12 months as the dependent variable will be performed. Secondary outcomes at 12 months will be treated in a similar way to the primary outcome; of the secondary outcomes, adherence will be measured at the 6-month point as well as the 12-month point.

A number of sensitivity analyses for the primary outcome are planned to be carried out. Regression models will be re-estimated including possible confounders such as participant characteristics that differ at baseline and may be associated with outcome (e.g. age, gender, duration of illness, socioeconomic status and education) and CHW characteristics like education and caseload; imputation of missing baseline covariates will be performed if there are more than 10% missing and analyses will be repeated.

Subgroup analyses will include site and gender as interactions with treatment arm to estimate differential effects, and further analyses will investigate the effect of engagement with the interventions on outcome. In addition to the primary intention-to-treat analysis, the effect of participants in the CCBC arm receiving the minimum effective number of sessions as defined in the protocol will also be estimated. Power for these subgroup analyses has not been specifically allowed for, and so they will be treated as exploratory.

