##### Outcome assessments

###### 1. Quantitative assessments

For the primary outcome assessments, we will record the *symptoms of schizophrenia *at baseline and at 12 months, with the Positive and Negative Syndrome Scale (PANSS) [17].

For measuring the *change in disability*, we will use the Indian Disability Evaluation and Assessment Scale (IDEAS)[18] at baseline, 6 and 12 months to generate information on the time course of the effect of the intervention.

For the secondary outcome assessment for persons with schizophrenia, we will measure:

• *Adherence with antipsychotic medication*: For each participant, we will assess adherence at baseline (if on treatment) and at 6 and 12 months using a 5 point ordinal scale developed for the study.

• For measuring *various dimensions of the experience of stigma and discrimination*, we will use the Discrimination and Stigma Scale (DISC)[19] at baseline and at 12 months.

• An item on *willingness to disclose mental illness *[20] will be used for participants at baseline and at 12 months to assess their readiness to disclose their illness.

• The Alienation subscale of the Internalized Stigma of Mental Illness (ISMI) scale[21] will be used to measure the *subjective experience of internalized stigma of participants *at baseline and at 12 months.

• Finally, to estimate the *Quality Adjusted Life Years (QALY)*, we will use the widely used Euroqol (EQ-5D) [22] at baseline and at 12 months.

**The secondary outcome measure for the **primary care givers are:

• The *family burden of caring *will be measured at baseline and at 12 months by using the Burden Assessment Schedule (BAS) which has been developed and used widely in India[23].

• The *knowledge and attitudes of family members about schizophrenia *will be assessed at baseline and at 12 months by using the Knowledge about Schizophrenia Interview (KASI) [24]

• A section of the 'Family Interview Schedule' (FIS) developed for the International Study of Schizophrenia (ISOS)[25] and previously used in a study in India[26] will be employed to assess *the experiences of stigma and discrimination experienced by the primary caregivers*.

• The item on *willingness to disclose mental illness *[20]will be used for caregivers after suitable modification.

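### The set called intention-to-treat is, for PANSS, an available-case set of 12-month responders, and no named analysis tests the missing-outcome assumption this brings

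*Protocol article*

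**What the plan says.** All references are to the protocol article.

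- **Analysis set** (Data management and analysis): the intention-to-treat principle is glossed as "all those with at least one follow up measurement will be analysed in arms as randomised".
- **PANSS schedule** (Outcome assessments, 1. Quantitative assessments): symptoms are recorded "at baseline and at 12 months, with the Positive and Negative Syndrome Scale (PANSS"). Table 2 agrees and marks no 6-month PANSS.
- **PANSS model** (Data management and analysis): "The 12-month PANSS total score, adjusted for PANSS scores at baseline and site (using analysis of covariance), and including clustering effects of CHWs". A logistic model of more than 20% PANSS reduction at 12 months is also planned.
- **IDEAS schedule** (1. Quantitative assessments): "at baseline, 6 and 12 months to generate information on the time course of the effect of the intervention".
- **IDEAS model** (Data management and analysis): the same form of analysis as PANSS and, in addition, "a longitudinal analysis including both 6- and 12-month outcomes will also be performed using a GEE or random effects model".
- **Missing data** (Data management and analysis): "imputation of missing baseline covariates will be performed if there are more than 10% missing". Scale totals are pro-rated when no more than 20% of items are absent.
- **Attrition** (Sample size estimation): the required 241 was "increased to 282 to allow for 15% attrition".

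**The concern.** A set defined by having at least one follow-up sounds as though it keeps nearly everyone. For an outcome with one follow-up visit it does not. A participant seen at 6 months and lost by 12 meets the definition but has no value to enter in the PANSS ANCOVA. The label therefore promises more than the model delivers, and the assumption that the model needs is not stated.

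The missing-data provisions address other gaps. Baseline assessments are finished before randomisation (The flow of participants in the trial), so baseline covariates are the data least likely to be absent. Pro-rating repairs an incomplete scale, not a missed visit. The outcome itself, for which 15% loss is expected, is covered by neither.

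At stake is possible bias in a primary comparison. Inflating the sample for attrition restores precision but does nothing about who is lost. Secondary outcomes are to be treated like the primary one, so they inherit the same feature.

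**Working it through.** **1. The plan's own figure.** 241 / (1 − 0.15) = 283.5, or 284 rounded up, against the stated 282. The attrition implied by 241 of 282 is 1 − 241/282 = 14.5%. The stated figure is reproduced to within 2 participants, and sample size is not the issue here.

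**2. How many leave the PANSS model.** With 188 CCBC, 94 FBC and 15% loss:
- CCBC: 0.15 × 188 = 28.2
- FBC: 0.15 × 94 = 14.1
- Total: 42.3 of 282, leaving 239.7, or about 240.

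**3. Who can enter each planned model.**

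| Seen at | Meets the stated definition | PANSS ANCOVA | IDEAS 12-month ANCOVA | IDEAS 6/12-month model |
|---|---|---|---|---|
| 6 and 12 months | yes | yes | yes | yes |
| 12 months only | yes | yes | yes | yes |
| 6 months only | yes | no | no | yes |
| neither | no | no | no | no |

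The third row shows the mismatch between the definition and the two 12-month models.

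**4. What the pro-rating rule covers.** PANSS has 30 items, so the rule reaches at most 0.20 × 30 = 6 missing items. It cannot supply a total for a visit that did not happen.

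**5. Size of a possible shift.** Let d be the proportion lost in an arm and g the amount by which non-completers would score worse than completers in that arm, after adjustment for baseline PANSS and site. The difference (CCBC − FBC) in all randomised participants equals the completer difference plus

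d(CCBC) × g(CCBC) − d(FBC) × g(FBC).

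The article gives neither loss by arm nor g, so the values below are assumptions. Each pair of losses is chosen to average 15%:
- 12% and 21%: (188 × 0.12 + 94 × 0.21)/282 = 42.3/282 = 15%
- 10% and 25%: (188 × 0.10 + 94 × 0.25)/282 = 42.3/282 = 15%

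| Loss CCBC v FBC | Gap g | Absolute shift (PANSS points) |
|---|---|---|
| 12% v 21% | 4.5 in both arms | 0.09 × 4.5 = 0.41 |
| 12% v 21% | 9 in both arms | 0.09 × 9 = 0.81 |
| 10% v 25% | 4.5 in both arms | 0.15 × 4.5 = 0.68 |
| 10% v 25% | 9 in both arms | 0.15 × 9 = 1.35 |
| 15% v 15% | equal in both arms | 0 |
| 15% v 15% | 4.5 to 9 in one arm, 0 in the other | 0.68 to 1.35 |

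The last row shows that equal loss is no guarantee: the gap must be equal too. Higher PANSS is worse, so heavier FBC loss with worse non-completers would make completers understate the CCBC benefit. Swapping the losses, or having better non-completers, reverses the sign.

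**6. Against the planned effects** (Sample size estimation).
- Largest shift: 1.35/13 = 10% and 1.35/7.2 = 19%.
- Smallest non-zero shift: 0.405/13 = 3% and 0.405/7.2 = 6%.
- On the baseline-adjusted SD of 9, the range is 0.045 to 0.15 SD.

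**The case against.** The strongest reply is that handling of missing outcomes normally belongs in an analysis plan, which is not shown. The article does not call its sensitivity analyses exhaustive and nowhere says outcomes will not be imputed. It also states openly who is analysed. This stands in part: one cannot conclude that missing PANSS scores will never be imputed. But the article itself fixes the set, the label, the model and a list of sensitivity analyses, and these do not fit an outcome with one follow-up.

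Four stronger readings are tempting, and the document does not support them.

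- **That the trial is unmasked.** Participants, caregivers and treating psychiatrists know the allocation. Outcome researchers are to be kept blind, with listed safeguards (Outcome evaluation/masking).
- **That loss will differ by arm because only CCBC has up to 22 community health worker (CHW) contacts.** Those contacts are treatment sessions. Follow-up in both arms is done by a research team separate from the intervention team, and facility care continues in both. Unequal, outcome-related loss is possible but not shown. Unequal loss alone does not bias an ANCOVA that includes arm.
- **That IDEAS has no protection.** The longitudinal model would use a 6-month value. The weakness is that the 12-month ANCOVA does not, and that the additional model is left open.
- **That the GEE option requires data missing completely at random.** An unweighted GEE also tolerates loss that depends on covariates in the model, such as arm, baseline score and site. It is exposed when loss depends on the 6-month outcome, where a correctly specified likelihood-based model is not.

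Two further objections are fair and shape the remedy. Imputing from arm, baseline PANSS and site alone would add essentially nothing to the ANCOVA, so any gain rests on auxiliary data that some non-completers will lack. And psychiatrist-rated CGI-SCH change comes from unblinded raters, so it could carry their knowledge of allocation into a blinded outcome.

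**Conclusion.** The point holds in a bounded form. For PANSS, the set described as intention-to-treat is an available-case set of 12-month responders, about 240 of 282 if the 15% planning allowance is met. The result is unbiased only if loss is unrelated to outcome given arm, baseline PANSS and site. The article neither states that condition nor names an analysis that tests it. The 12-month IDEAS ANCOVA has the same limitation for people seen only at 6 months, softened by the additional longitudinal model.

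The illustrated shift is 0 to 1.35 PANSS points, or about 0.4 to 1.35 where the assumed losses differ by arm. It rests wholly on assumed losses and assumed residual gaps, and its direction cannot be predicted. It is small against the 13-point target and reaches 19% of the 7.2-point effect at most. This warrants correcting the description and adding an analysis. It does not show that the trial's conclusion would be wrong.

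**What to change.** 1. **Wording.** Describe the PANSS analysis as available cases analysed as randomised, and state its assumption: loss unrelated to the 12-month score given arm, baseline PANSS and site.
2. **PANSS, all 282 randomised.** Add multiple imputation carried out separately by arm, using data already scheduled: baseline PANSS and IDEAS, site, 6-month IDEAS and adherence, and inpatient stay. Follow it with a delta-adjusted sensitivity analysis in which the shift applied to imputed scores can differ by arm.
3. **CGI-SCH change.** Use the psychiatrists' ratings only in a sensitivity version of the imputation, because those raters are unblinded.
4. **IDEAS.** Take the 12-month contrast from the 6- and 12-month model already planned, and settle the open choice ("using a GEE or random effects model including a time x treatment term") as a likelihood-based random-effects model, so that people with only a 6-month value contribute.

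The cost is revised wording and some extra analysis work. No new data and no change in sample size are needed. The downside is reliance on a missing-at-random model, which the delta adjustment probes but cannot verify.

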**Methods/Design:**

This trial is a multi-site, parallel group randomised controlled trial design in India.

The trial will be conducted concurrently at three sites in India where persons with schizophrenia will be screened for eligibility and recruited after providing informed consent. Trial participants will be randomly allocated in a 2:1 ratio to the CCBC+FBC and FBC arms respectively using an allocation sequence pre-prepared through the use of permuted blocks, stratified within site. The structured CCBC intervention will be delivered by trained lay community health workers (CHWs) working together with the treating Psychiatrist. We aim to recruit 282 persons with schizophrenia. The primary outcomes are reduction in severity of symptoms of schizophrenia and disability at 12 months. The study will be conducted according to good ethical practice, data analysis and reporting guidelines.

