### Objectives

The objectives of the trial are: firstly, to test the hypotheses that usual, Facility-Based Care (FBC), when combined with a Collaborative Community-Based Care intervention (CCBC), will be superior to Facility-Based Care alone in improving a range of outcomes in people with schizophrenia and their caregivers and, secondly, to determine if the CCBC intervention is cost effective in India.

The primary objectives of the trial are to determine whether the FBC+CCBC intervention will be superior to FBC alone in:

i) reducing symptoms of schizophrenia at 12 months, and

ii) reducing disability related to schizophrenia over 12 months.

In *persons with schizophrenia*, the secondary objectives are to determine whether, FBC+CCBC will be more effective than FBC alone, in:

• improving adherence to antipsychotic treatment

• reducing experiences of stigma and discrimination

For *caregivers of people with schizophrenia*, the secondary objectives are to determine

whether, FBC+ CCBC will be superior to FBC alone, in:

• improving their knowledge and attitudes about the illness

• reducing their burden of caring

• reducing experiences of stigma and discrimination.

The health economic objective is to compare the costs and assess the cost-effectiveness and cost-utility of the FBC+ CCBC intervention compared to FBC alone.

The COPSI trial is a collaborative effort between multiple institutions and individual Psychiatrists at the Indian sites. The lead institution is the Institute of Psychiatry (IoP), Kings' College, London, while the partner organizations are the London School of Hygiene and Tropical Medicine (LSHTM), Sangath in Goa, the Schizophrenia Research Foundation (SCARF) in Chennai, the National Institute of Mental Health and Neuroscience (NIMHANS) in Bangalore and Parivartan and Nirmittee in Satara. In Goa and in Satara, the individual collaborators are Psychiatrists working in the private sector.

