• The *caregiver summary assessment of the participant's degree of adherence *will be rated by using the same 5 point ordinal scale used for participants. To improve the validity of adherence ratings, we will complete a systematic assessment of medication use for the last 2 months (to minimize recall bias over the 6 month period); this 2 month adherence will be extrapolated for the last 6 months.

For the economic aspects of the study, we will ask caregivers to complete the Cost of Illness Schedule (CIS) that has been developed and used in India in community studies before[27] at baseline, 6 and 12 months. In addition, we will record the type, dosage and duration of medications prescribed by treating Psychiatrists during each of the contacts with participants as well as the number of inpatient days for each participant - this data will be available from the Psychiatrists' structured records. Service costs will be calculated by attaching locally calculated unit costs to these data. In addition, we will use the Euroqol EQ-5D with participants for assessing Quality of Life Years at baseline and at 12 months.

The adherence measures and the CIS will be repeated at 6 months, as will the IDEAS. For the CIS and adherence measures, the rationale is to minimize recall bias. The IDEAS will be used at 6 months to have an interim measure for one of the primary outcomes that is brief and easy to complete.

Table 2 describes the data collection details of the study.

**Table 2 T2:** Summary table of data collection in COPSI.

TYPE OF DATA					
**1. Quantitative**: (using a combination of programmed palmtops and paper and pencil methods)			**Measured at**:		

**Primary Outcome**	**Interviewee**	**Outcome assessment scale description**	**0 month**	**6 months**	**12 months**

Symptoms	Person with schizophrenia	*Positive and Negative Syndrome Scale (PANSS)*. The PANSS has 30 items to record current psychopathology on 3 domains- positive symptoms, negative symptoms and general psychopathology; each item rated on 1-7 scale thus having a total score range of 30-210.	**X**		**X**

Disability	Primary caregivers	*Indian Disability Evaluation and Assessment Scale (IDEAS)*. For the IDEAS evaluation, the participant is assessed on 4 domains- Self Care, Interpersonal Activities, Communication and Understanding and Work. The scale generates a global score of 0-20 with increasing scores indicating more severe disabilities	**X**	**X**	**X**

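### The primary disability outcome has two time frames, and its 12-month ANCOVA leaves out participants seen only at 6 months, whom the intention-to-treat set includes

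*Protocol article*

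**What the plan says.** All places are in the Protocol article.

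- **Abstract, Methods/Design:** "The primary outcomes are reduction in severity of symptoms of schizophrenia and disability at 12 months".
- **Objectives:** the symptom objective reads "reducing symptoms of schizophrenia at 12 months, and" and the next line gives disability as "reducing disability related to schizophrenia over 12 months".
- **Quantitative assessments:** IDEAS is recorded "at baseline, 6 and 12 months to generate information on the time course of the effect of the intervention". Later in the same section: "The IDEAS will be used at 6 months to have an interim measure for one of the primary outcomes".
- **Data management and analysis, symptoms:** the analysis variable is "The 12-month PANSS total score, adjusted for PANSS scores at baseline and site (using analysis of covariance), and including clustering effects of CHWs".
- **Data management and analysis, disability:** "The disability score generated by the IDEAS will be similarly analysed". A second, supplementary model is then described: "a longitudinal analysis including both 6- and 12-month outcomes will also be performed using a GEE or random effects model including a time x treatment" interaction.
- **Data management and analysis, analysis set:** intention-to-treat is defined as everyone with one or more follow-up assessments, kept in the arm to which they were randomised.
- **Sample size estimation:** 241 required, raised to 282 for 15% attrition, split 188 to 94.

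**The concern.** Disability is one of two primary outcomes, and the protocol gives it two time frames and two analyses without saying which result answers the objective.

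The practical consequence lies in the analysis set. PANSS has a single follow-up at 12 months, so for PANSS the set and the analysis agree. IDEAS has follow-ups at 6 and 12 months. A participant with IDEAS at 6 months only belongs to the stated set but cannot enter an ANCOVA of the 12-month score. The two planned IDEAS analyses would therefore run on different people, and the one modelled on the PANSS analysis would discard information already collected on participants who later drop out. If dropout after 6 months is related to how disabled the participant was at 6 months, the 12-month ANCOVA can be biased where a model that uses the 6-month score need not be.

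**Working it through.** **1. The plan's own figure.** 241 / 0.85 = 283.5, so 284; the plan states 282, which is 3 × 94 and so fits 2:1 allocation. 282 × 0.85 = 239.7. The difference of 2 is immaterial. About 240 participants (160 v 80) are expected at 12 months.

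**2. How many are affected.** 282 × 0.15 = 42.3. Of about 42 without a 12-month score, the number with a 6-month score is not given. The range is 0 to 42, or 0% to 15% of those randomised.

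**3. Precision.** Suppose every retained participant has both visits and all of the lost 15% have a 6-month score. With ρ the correlation of the baseline-adjusted 6- and 12-month scores, the likelihood estimate of a 12-month mean has large-sample variance (σ²/n₁₂) × [1 − ρ² × 0.15], against σ²/n₁₂ for the ANCOVA.

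- ρ = 0.4: 1 − 0.16 × 0.15 = 0.976, so the SE is multiplied by 0.988.
- ρ = 0.8: 1 − 0.64 × 0.15 = 0.904, so the SE is multiplied by 0.951.

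The best case is thus a reduction of 1% to 5%; ρ is an assumption.

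**4. Bias.** Suppose that in one arm only, the lost 15% had adjusted 6-month scores k SD worse than those retained. The retained group's 6-month mean is off by 0.15k, and its 12-month mean, hence the arm contrast, by ρ × 0.15k. With k = 0.5 this is 0.4 × 0.075 = 0.03 SD to 0.8 × 0.075 = 0.06 SD. It scales with k, and k is an assumption.

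**5. What the longitudinal model estimates.** Take 6- and 12-month IDEAS as outcomes, baseline as covariate and 6 months as reference visit. The arm coefficient is then d₆ and the arm-by-time coefficient is d₁₂ − d₆. The 12-month effect is their sum, and the average effect is the arm coefficient plus half the interaction. One fit gives all of them.

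**6. Illustrative power of each contrast.** The protocol gives no IDEAS effect size or SD. Assumed: 160 v 80, adjusted SD 1, d₁₂ = 0.4, ρ = 0.5, two-sided 5%, no clustering.

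- SE(12 months) = √(1/160 + 1/80) = 0.137
- SE(average) = 0.137 × √((1 + ρ)/2) = 0.119
- SE(interaction) = 0.137 × √(2(1 − ρ)) = 0.137

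| 6-month effect | 12-month contrast | Average | Interaction |
|---|---|---|---|
| Equal (0.4) | 83% | 92% | 5% |
| Half (0.2) | 83% | 72% | 31% |
| Zero | 83% | 39% | 83% |

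With within-CHW ICC 0.05 and 20 participants per CHW, the CCBC design effect is 1 + 19 × 0.05 = 1.95. The 12-month power becomes 72%, and the average 84%, 60% and 31%.

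A simulation with a constant effect of 0.5 SD and ρ = 0.6 (300 replicates) agrees in pattern. The 12-month ANCOVA rejected in 96.7%, the average in 99.3% and the interaction in 4.0%, with a mean interaction estimate of −0.002.

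**The case against.** **The mismatch is only wording.** The article also uses the same phrase loosely for the length of follow-up and for the period in which sessions are delivered. The 6-month IDEAS is called an interim measure, and the abstract says 12 months. A 12-month endpoint is the natural reading. This stands: the mismatch alone is close to clerical. A reader might infer that the Objectives deliberately set an average over the year as the target, but nothing in the protocol defines one.

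**A sustained effect could look null.** A reader might infer this because the interaction is zero when the effect is equal at 6 and 12 months. The protocol does not support it. It never names the interaction as the test of effect; the longitudinal model is additional and meant to describe change over time, for which that term is suitable. The 12-month ANCOVA would detect a sustained effect (83% in the table), and the 5% for the interaction is correct type I error for a different question.

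**Participants seen only at 6 months are not lost to the plan.** The longitudinal model can use them, and the analysis-set sentence covers several outcomes. This stands in part. They still drop out of the analysis that mirrors the PANSS one, and the protocol does not give the longitudinal model precedence.

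**The choice of model is detail for the analysis plan.** Visit coding and the way baseline enters can be left there. The time frame of a primary outcome, and a set that its analysis cannot accommodate, are stated in this article and can be corrected in it.

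**Conclusion.** The point holds in limited form. The time frame of the primary disability outcome is inconsistent between the abstract and the Objectives, and the 12-month IDEAS ANCOVA cannot be run on the intention-to-treat set that the protocol defines. It affects at most about 42 of 282 participants, and possibly far fewer. The gain is modest: at best a 1% to 5% smaller standard error, and protection against a bias of some hundredths of an SD in the example shown. It is worth having because the change is almost free and concerns a primary outcome.

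Two readings underlie this. That the main IDEAS analysis is a 12-month ANCOVA is inferred from its being treated like the PANSS. That baseline is a covariate in the longitudinal model, not an outcome row, is favoured by the wording but not fixed by it. The power figures are illustrative and show only that the contrasts answer different questions.

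**What to change.** 1. In the Objectives, give the disability outcome at 12 months, to match the abstract.
2. In the analysis section, make the primary disability result the 12-month arm contrast from one likelihood-based repeated-measures model. Outcomes: 6- and 12-month IDEAS. Terms: baseline IDEAS, site, visit, arm and arm by visit. Allow for correlation between visits and clustering by CHW.
3. Report the 6-month contrast and the arm-by-visit interaction as secondary descriptions of time course.
4. Keep the 12-month ANCOVA as a sensitivity analysis. When every participant has both visits, the two should give nearly the same 12-month contrast.

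The cost is wording, analysis code and a slightly more complex model. The result then relies on data being missing at random given baseline, arm, site and the 6-month score. The 12-month ANCOVA needs a stronger assumption, because it cannot condition on the 6-month score. Choosing a likelihood-based model also settles the open choice between GEE and random effects; ordinary unweighted GEE does not in general carry the same protection. The 6-month IDEAS is already collected, so no new data are needed.
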